**Fig. 1 Fig1:**
[figure not shown]
Causal Model

Our secondary aim is to explore the differential effectiveness of the two interventions by baseline cognitive functioning and age. Because integrated treatment programs like CET were designed to reduce the moderating effects of impaired cognition on response to social skills training [20, 23], we predicted that *poorer baseline cognitive functioning* will be associated with *greater treatment response* for patients who receive CET as compared to those who receive SST (which doesn’t seek to increase cognitive functioning) [32, 37, 49–56]. Given that the younger brain retains neuroplastic reserves that may make it uniquely capable of benefiting from cognitive remediation [57–59], we also predicted that younger participants would benefit more from CET than older ones, while the same interaction with age would not occur for SST recipients [60–62]. Variation across our treatment delivery sites (approximately 24) in treatment dose may also influence the effectiveness of both interventions, with individuals attending more treatment sessions—even when it is due to challenges at the site rather than orientations of the participants—potentially benefiting more from the treatment.

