### Trial design

Project SUCCESS is a comparative effectiveness trial of Cognitive Enhancement Therapy (CET), a combined treatment offering both CR and features designed to improve social functioning, with Helping Ourselves Pursue and Experience Success (HOPES), a treatment that offers only SST. The study uses a cluster-randomized design to allocate participating treatment sites to provide either CET or HOPES in groups of 6-8 eligible participants for 12 months of treatment, with post-treatment assessments of functioning conducted up to 12 months post-treatment. Most sites will offer two successive treatment groups.

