### Study interventions

*Cognitive Enhancement Therapy* is a comprehensive cognitive remediation program designed to maximize gains in social functioning by integrating computer-based training to enhance neurocognition with group-based exercises to improve social cognition [22, 43, 45, 57]. CET facilitates the development of adult social-cognitive milestones (e.g., perspective-taking, social context appraisal) by shifting thinking from reliance on effortful, serial processing to a “gistful” and spontaneous abstraction of social themes. All procedures are described in a step-by-step manual followed by CET trainers [45]. CET’s group-based exercises are delivered for 1.5 hours each week in a group of 6-8 participants led by two clinicians. During each of three modules (basic concepts, social cognition, CET applications), the group focuses on acquisition of adult social milestones in perspective-taking, social context appraisal, and other aspects of social functioning, with psychoeducational lectures on topics ranging from the neurobiology of schizophrenia to the concept of self-defeating thinking, homework assignments, and in-group exercises. CET’s computer-based training is supervised by a clinician who meets weekly for one hour with a pair of participants who make progress on an attention, memory, or problem-solving exercise in each session. The paired participants take turns practicing exercises on a computer, providing encouragement and advice to each other, as the clinician provides strategy coaching and support.

*Social Skills Training*: HOPES is a manualized SST rehabilitation program that is delivered over a 12-month period, with weekly group skills classes and monthly community practice trips and engagement of natural supports to facilitate skill use in real-world situations. HOPES classes are conducted using the principles of SST (modeling, role playing, positive and corrective feedback, in vivo assignments), some of it adapted from the Bellack et al. [63] curriculum. The curriculum is organized into eight topic areas or “modules”: Living Well in the Community, Communicating Effectively, Making and Keeping Friends, Making the Most of Leisure Time, Using Medications Effectively, Healthy Living, Intimacy and Dating, and Making the Most of a Doctor’s Visit. Each module includes 6–8 component skills, with one skill covered each week. HOPES is standardized in a manual and a participant workbook with handouts for each skill [48].

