Specifically, we will compute change scores (amount of improvement) from baseline to 18 months (for all subjects), and from baseline to 24 months (for 3/4 of subjects) for both primary outcomes and mediators for mediation analysis. For primary (or marginal) mediation analyses, we will estimate total effect of the treatment (TE), which can be decomposed into direct treatment effect (called natural direct effect, NDE) and indirect (or mediated) effect (called natural indirect effect, NIE); that is, TE = NDE + NIE with two-way decomposition. Bootstrap methods will be used to estimate standard errors and confidence intervals for mediation effects. A major advantage of the causal mediation method is that it allows testing and controlling for potential confounding effects due to non-random assignments of the mediators. With this approach, the percentage mediated effect can also be calculated. To test mediated effects potentially moderated by baseline cognitive function (high vs. low) and age category (young vs. old), moderated causal mediation analysis will be conducted to examine whether mediation patterns are the same for subgroups defined by moderators. Magnitude and percent of mediated effect between the subgroups (conditional causal mediation effect) will be compared.

Variation between our patients and across our treatment delivery sites in patient engagement may also influence the effectiveness of both interventions. We expect that greater treatment dose (sessions attended) will multiply gains in treatment impact on community functioning and quality of life for both CET and SST, thus moderating the impact of treatment along both primary causal pathways, but not changing predictions of the relative effectiveness of CET compared to SST.

As our HTE analyses are not based on testing explanatory hypotheses, we will report the corresponding *p*-values for hypothesis testing for these subgroup analyses. However, rather than relying on statistical significance testing alone, we will evaluate HTE using a combination of statistical significance and clinically meaningful difference with emphasis on the magnitude of treatment effects with standard errors (clinically meaningful effect sizes) as outlined in PCORI Methodology Standards [95] and recommended by statisticians [96].

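### Individual session attendance is given a causal moderating role in exploratory Aim 2, although it arises after allocation and partly reflects prognosis, so a dose effect can appear where none exists

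*Protocol article*

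**What the plan says.** All references are to the protocol article.

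- **Analysis for Aim2 (HTE or moderation effect).** Dose is defined as sessions attended and given a direction and a role: "We expect that greater treatment dose (sessions attended) will multiply gains in treatment impact on community functioning and quality of life". The same sentence says that dose thereby moderates the effect of treatment on each of its main causal routes, "but not changing predictions of the relative effectiveness of CET compared to SST". The source of the variation is named just before: "Variation between our patients and across our treatment delivery sites in patient engagement may also influence the effectiveness of both interventions".
- **Aims and hypotheses** (text after Figure 1). Participants who attend more may benefit more, "even when it is due to challenges at the site rather than orientations of the participants". Both sources of attendance, site and participant, are thus acknowledged.
- **Trial design.** "The study uses a cluster-randomized design to allocate participating treatment sites to provide either CET or HOPES". Dose is not allocated.
- **Process evaluation.** Sessions delivered and attended are logged for each participant. Interruptions caused by hospitalization go into the same engagement record.
- **Study interventions.** In CET, "CET’s group-based exercises are delivered for 1.5 hours each week in a group of 6-8 participants led by two clinicians", and in addition "CET’s computer-based training is supervised by a clinician who meets weekly for one hour with a pair of participants". HOPES runs "with weekly group skills classes and monthly community practice trips".
- **Missing data modeling.** Mixed models are to be used for testing every hypothesis.

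The Aim 2 section mentions control of confounding for the mediators only. It writes a model for two moderators, baseline cognition and age, and both are fixed before treatment starts.

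**The concern.** A moderator in the usual sense is fixed before treatment. Attendance is not. It accumulates over the same 12 months in which the outcome changes, and the article itself gives two ways in which it can follow prognosis: the participant's disposition, and hospitalization. A participant who is doing well is likely to attend more and to improve more, whether or not the extra sessions help.

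There is no untreated arm and no randomized variation in dose. A positive dose slope in both arms, which is the pattern the article predicts, is also what prognosis-driven attendance would produce. If such a slope is reported in the terms the article now uses, readers deciding how to spend scarce clinic resources could take it as evidence that more sessions cause more gain. The design does not support that.

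A second, smaller question is whether a session means the same thing in the two arms, since the scheduled contacts differ.

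**Working it through.** The article gives no figure for a dose analysis, so there is none to reproduce. The check asks how often a dose effect would be declared if the true effect were zero.

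**Inputs from the article.** N = 378, 20% attrition by 12 months, two-sided 0.05 (Sample size and power). Analysed N = 378 × 0.80 = 302.

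**Assumptions.** An unmeasured prognostic factor U has loading a on both latent attendance and outcome, so the induced correlation is a × a. Its size is not in the article, so a range is shown. Mean attendance is about 71% and delivery lasts 52 weeks. The simulation is a single end-point regression of outcome on arm and dose, with 2,000 to 4,000 runs per setting. It is not the full longitudinal mixed model.

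**Which test matters.** The article expects dose to raise gains in both arms without altering their relative standing. That corresponds to a dose slope common to both arms, not to an arm-by-dose difference.

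**Step 1: false-positive rate for dose** (share of scheduled sessions, arm in the model). The analytic column is Φ(z − 1.96) + Φ(−z − 1.96), with z = atanh(r) × √(302 − 3) = atanh(r) × 17.29.

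| a | Induced r | z | Analytic | Simulated |
|---|---|---|---|---|
| 0 | 0 | 0 | 5% | 5% |
| 0.1 | 0.01 | 0.17 | 5% | 6% |
| 0.2 | 0.04 | 0.69 | 11% | 9% |
| 0.3 | 0.09 | 1.56 | 34% | 34% |
| 0.4 | 0.16 | 2.79 | 80% | 78–79% |
| 0.5 | 0.25 | 4.42 | 99% | 99% |

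The two methods agree closely.

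**Step 2: does baseline adjustment help?** Same null, adding a baseline proxy for U.

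| Baseline proxy for U | r = 0.09 | r = 0.16 | r = 0.25 |
|---|---|---|---|
| None | 34% | 79% | 99% |
| Reliability 0.5 | 11% | 30% | 67% |
| Reliability 0.8 | 7% | 10% | 18% |
| U fully measured | 5% | 5% | 5% |

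Adjustment helps a good deal, but removes the bias only if the confounder is fully captured.

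**Step 3: site-mean dose instead of individual dose.** About 8%, 12% and 22% at the same three correlations, and 7% with no confounding. This is better than unadjusted individual dose, but not clean.

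**Step 4: unequal schedules.** Over 52 weeks, summing all components:

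- CET: 52 group + 52 computer = 104.
- HOPES: 52 classes + 12 trips = 64.
- Ratio 104/64 = 1.6. Full HOPES attendance equals 64/104 = 62% of the CET schedule.

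The effect on error rates depends on the model:

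- Raw counts, arm in the model: 33%, 75% and 98% at r = 0.09, 0.16 and 0.25, almost the same as with shares. The unequal count adds nothing.
- Raw counts, arm omitted, CET truly better by 0.34 SD, no confounding and no dose effect: dose significant in 44% of runs.
- Arm-by-dose term on raw counts: 9% at r = 0.16 and 15% at r = 0.25, against about 5% with shares.

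**The case against.** The strongest reply is that the article states an expectation and not an analysis. The Aims text says only that dose may matter. No dose model, pooled session count or split of attendance is written, and the Aim 2 model is set out for baseline cognition and age alone. Aim 2 is labelled exploratory, and the article says it will weigh effect sizes alongside p-values. The dose metric and covariates could properly sit in a fuller plan that is not shown.

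Much of this stands. The lack of a detailed dose model is not itself a fault, and dose should not be called a formal objective. What remains is what the article does fix: the variable, the outcomes and a causal moderating role, in the analysis section, with mixed models announced for every hypothesis test. The exploratory label and the false discovery rate correction deal with multiplicity. They do nothing about confounding.

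A reader might infer several stronger things that the documents do not support:

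- **That the trial is bound to report a spurious dose effect.** With weak confounding the error rate stays near its nominal level, and the strength of confounding is unknown.
- **That differing session counts are enough to spoil the analysis.** The Aim 2 models are described as the Aim 1 models, which contain arm, and with arm included the unequal counts add almost nothing. Nothing says that classes, computer hours and trips will be summed.
- **That an arm difference in the dose slope would be read as a property of treatment.** The article predicts no such difference.
- **That all attendance is self-selected.** Some of it is driven by the site, as the Aims text says.

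**Conclusion.** The point holds as a fault in the causal role given to patient-level dose. Sessions attended is a post-allocation, non-randomized variable that partly reflects prognosis, and no safeguard is stated for it. If dose has no true effect, the analysis can show one, and with moderate confounding probably will: about 5–9% at induced correlations of 0 to 0.04, then 34%, 79% and 99% at 0.09, 0.16 and 0.25. These rates rest on an assumed confounding strength, 302 analysed participants and a simple end-point regression. They show sensitivity and are not a forecast.

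The unequal schedules (about 104 and 64 contacts, given 52 weeks and all components summed) are secondary. They matter only if arm is omitted or raw counts enter an arm-by-dose term.

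It would be wrong to carry the point over to the main result. Analyses for Aim 1 include everyone regardless of exposure, so the randomized comparison of CET with HOPES is untouched. What changes is the conclusion the trial can draw about dose.

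**What to change.** In Aims and hypotheses and in the Aim 2 analysis section:

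1. Drop the statement that patient-level dose multiplies or moderates the treatment effect.
2. Report dose as a non-causal association. Measure it as the share of the arm's own scheduled sessions that the participant attended, keep arm in the model, and adjust for baseline functioning, symptoms and cognition.
3. Show dose delivered at site or group level separately, as a supplementary exploratory analysis. It should not replace the patient-level description: it is not randomized either, it varies over only about 24 sites or 51 groups, and the related site-mean measure still gave 8–22% false positives in the check above.

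The cost is wording and a small amount of analysis, since site research assistants already log sessions delivered and attended. The downside is that the dose result supports a weaker conclusion, and residual confounding remains after baseline adjustment. The report should say so.

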#### Adjusting for multiple subgroup comparisons

Subgroup analysis for treatment effects (i.e., estimate of the treatment effect for each subgroup) is a common approach for HTE analysis, but it is susceptible to the issue of multiple post hoc analyses. For the analyses of primary and secondary hypotheses, it is necessary to control for possible Type I error due to multiple tests. However, our moderation analyses will test exploratory hypotheses, and thus we will report the results of statistical tests including both corrected and uncorrected probability levels. To this end, we will adjust the *p*-value to account for multiple tests for each subgroup analysis using the false discovery rate method [97] implemented in SAS software [98]. Subgroup analysis may also increase the likelihood of Type II error due to small sample sizes. Therefore, we will not rely on statistical tests and *p*-values alone to evaluate HTE; we will also examine estimated effect sizes (estimate divided by the standard deviation) and compute confidence intervals around these effect sizes.

#### Missing data modeling

We will use generalized linear mixed modeling (GLMM) to test all hypotheses. The GLMM uses all available data, thus allowing intermediate missing data and attrition in the outcome vector. GLMM yields valid inferences, assuming data are missing at random (MAR). However, it is possible that some outcome data may not be missing at random. Thus, it is important to test the MAR assumption. Because the distinction between MAR and not missing at random (NMAR) involves unobserved data, we cannot test whether the missing pattern is MAR or NMAR using the collected data [99]. We will use multiple empirical ways to check the MAR assumption, and to ensure stability of our estimates and inference. In addition, we will conduct sensitivity analyses using several NMAR models (e.g., selection model and pattern mixture model) [100] to see if the results from different NMAR models are consistent from our MAR model. At a minimum, we will check to see if the patterns and rates of attrition are different across intervention arms; if we find this to be true, we will use a pattern mixture model to refit our models and to evaluate potential biases associated with missing data.

Throughout, we used the SPIRIT reporting guidelines [101].

## Stakeholder engagement

The project leadership structure includes four groups: The Project Leadership Group, the combined Project Steering Committee, the Stakeholder Committee, and the Training and Implementation Team (CET and SST) (see Fig. 3). Local stakeholder representation is provided by the preexisting Consumer Advisory Board (CAB) at the Massachusetts Mental Health Center (MMHC)—where the study is headquartered within the BIDMC system—and by local stakeholder groups at other sites.

**Fig. 3 Fig3:**
[figure not shown]
Project Leadership and Stakeholder Structure

The Leadership Group is responsible for general project oversight, project planning, and management of implementation, training, treatment, engagement, and assessment, as well as planning study-related publications. Throughout the study, weekly meetings of the co-PIs and the entire co-investigator group and monthly meetings of the site PI group ensure coordination of all project activities and timely response to any challenges. Our lead consumer consultant will provide guidance as a cultural broker to ensure effective communication with participants and to maintain an appropriate balance of power throughout the project.

The Project Steering Committee provides overall project guidance in a collaborative structure that maximizes shared learning and site-specific lessons. This Committee’s annual meeting brings together the Project Leadership Group, the site PIs, and the Stakeholder Committee representatives to ensure multiple perspectives on project activities and critical engagement about project challenges. Many of the site PIs are very experienced researchers and all are experts in service design and delivery, while members of our Stakeholder Committee represent a wealth of experience in different service delivery systems and with different roles in the treatment system. At the project’s conclusion, a combined Stakeholder and Steering Committee meeting will present main research findings, provide breakout groups for discussion and interpretation, and plan publications.

The co-PIs will lead monthly virtual meetings of the site PIs to ensure flexible and timely response to site-specific challenges in implementation, management, and engagement as well as to maximize sharing of strategies and perspectives and communication of results.

A broad spectrum of stakeholders representing lived experience, advocacy, and organization and delivery of services will provide advice and feedback to guide the direction of the project so that the most effective interventions can be implemented widely following conclusion of the PCORI-sponsored project. Our Stakeholder Committee begins with 13 members representing 11 different locations and the perspectives of people with lived experience of mental illness (7 members), family members (2 members), and professionals (4 members). The Stakeholder Committee members will have two annual virtual meetings to review project progress, seek feedback about challenges to recruitment, data collection and other project activities, and discuss what we have learned from treatment delivery and preliminary analyses. Meetings will also address any site-level barriers to conducting the study.

The MMHC Consumer Advisory Board (CAB) represents a partnership between people with research, clinical and/or lived experience with SMI. The CAB at our project headquarters provides a unique local opportunity to elicit and receive feedback from individuals with lived experience who are not involved in the conduct of the study and are therefore able to offer suggestions and advice that may not occur to those who are project participants. These individuals already have deep experience in participatory clinical research. The MMHC CAB will review project reports at one meeting each quarter to provide regular and frequent input into recruitment, retention, intervention delivery, questions for qualitative interviews on treatment process, and suggestions for data analysis.

Patient representatives and advocates on the Steering Committee will hold semiannual meetings with the local stakeholder groups to review and inform treatment and research plans. We consider these meetings to be a vital part of our plan to manage our project in a way that reflects the values of social connection and peer support that are reflected in the interventions themselves. The local stakeholder groups represent the strategies developed at unique sites to engage stakeholders and so will provide diverse perspectives on project issues that in turn will result in a more holistic understanding of project progress.

The process of synthesizing stakeholder feedback will be dynamic, responsive, and person-centered. Stakeholder committee members will present reports about local stakeholder groups (including the CAB) at the biennial Stakeholder Steering Committee meetings, as well as at the annual project Steering Committee meeting. An ongoing working group of Stakeholder Committee members will periodically review process evaluation and assessment data and suggest improvements in procedures and directions for analyses. Collaboration and partnership among these groups is facilitated by leadership provided by our consumer consultant, [name], and a Stakeholder Leadership Team that also includes one of the two co-PIs and two co-investigators [102].

When stakeholder feedback suggests or the Steering Committee participants recommend changes, the leadership team will propose actions and then seek review by the stakeholder groups. After taking feedback into account, the leadership team will publicize and implement the resulting recommendations. Any indications of adverse events and any protocol modifications are reported to (and must be approved by) the BIDMC CCI (IRB) and trial conduct is also monitored by PCORI in monthly meetings and semi-annual reports.

All co-investigators are expected to be co-authors of major project papers and will serve as an approval board to grant authorship to study staff, site-level principal investigators, and stakeholder committee members upon request and when warranted by expert contributions to specific articles.

